## Methods/design

### Study design

The study protocol was designed in accordance with the SPIRIT guidelines [38]. This is a 12-week, randomized controlled, parallel-group, multicenter trial of intradialytic NMES and protein supplementation for HD-dependent ESRD patients. Seventy-two patients receiving HD will be randomly assigned in a 1:1:1:1 ratio to the control, intradialytic NMES only, protein supplementation only, and intradialytic NMES combined with protein supplementation groups. Measurements will be scheduled for all patients at baseline and at follow-up every 4 weeks for 12 weeks; the measurements will include vital signs; blood and urine laboratory exams including total protein, albumin, total cholesterol, calcium, phosphorus, blood urea nitrogen (BUN), serum creatinine (SCr), total CO_2_, intact parathyroid hormone (PTH), highly sensitive C-reactive protein (hs-CRP), urine urea nitrogen/normalized protein catabolic rate (nPCR), and Kt/V; and body composition including bioelectric impedance study, physical performances, and questionnaires. Figure 1 presents a flowchart of the trial procedures.

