### Sample size

Sample size estimation was based on detecting a mean between-group difference in leg muscle strength at the end of the study. Based on the results from an earlier study [34], the rationale mean (pooled standard deviation (SD)) for calculating the sample size was 24.82 (we chose the left leg SD, which was larger than the right leg SD of that study, to approach conservatively). Therefore, the means (SDs) of leg muscles in the NMES and control groups were 26.1 (24.82) and −8.3 (24.82), respectively.

Assuming a two-tailed hypothesis, an alpha value of 0.0083 due to the correction for type 1 error according to multiple tests, and a desired power of 80%, 13 participants are needed per group to complete the study. To allow a 25% dropout rate, we will initially recruit at least 72 participants.

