### Statistical methods

The statistical processing will be performed with PASW advanced statistics (SPSS Inc, Chicago, IL) version 20.0 and according to an intention-to-treat principle. Data will be reported as the mean, standard deviation, and confidence intervals or in percentage frequencies. The Shapiro-Wilk test will evaluate the normal distribution of the variables. Evaluation variables, including muscle strength, performance tests, and questionnaire surveys, will be analyzed at baseline and after 4, 8, and 12 weeks by using paired *t*-tests or Wilcoxon signed-rank tests. Outcomes will be compared between groups by using two-sample *t*-tests or Wilcoxon rank sum tests according to normality. Analysis of covariance will also be conducted. The between-group differences in the outcome measures after the intervention will be calculated using repeated measure mixed models with patients as random effects, and group and time as fixed effects, and adjustments for baseline imbalances. The Spearman rank test or Pearson product-moment correlation coefficient analysis may be used to analyze the associations between clinical data and outcome measures. Statistical significance is set at a *p* value < 0.05. There is no plan for any interim analysis or stopping data collection. There are no planned subgroup analyses for any of the primary or secondary outcomes.

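### Thirteen completers per group give about 74% power for the planned two-sample t-test at alpha 0.0083, not the stated 80%

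*Protocol article*

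**What the plan says.** The Sample size section of the protocol article sizes the trial on leg muscle strength, NMES against control. It states that "the means (SDs) of leg muscles in the NMES and control groups were 26.1 (24.82) and −8.3 (24.82), respectively". The error rate is "an alpha value of 0.0083 due to the correction for type 1 error according to multiple tests", and the test is two-sided ("Assuming a two-tailed hypothesis"). The result is "a desired power of 80%, 13 participants are needed per group to complete the study", followed by "To allow a 25% dropout rate, we will initially recruit at least 72 participants". No formula or software is named for this calculation.

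On the analysis side, the Statistical methods section says: "Outcomes will be compared between groups by using two-sample" t-tests, or Wilcoxon rank sum tests where normality fails. It adds that analysis of covariance will also be done, and it describes a repeated-measures mixed model with baseline adjustment.

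**The concern.** The usual normal-approximation formula treats the SD as known. With about a dozen patients per arm that is a poor approximation, and it worsens as alpha shrinks, because the t distribution departs most from the normal in its tails. A trial sized at 13 per group and alpha 0.0083 is exposed on both counts.

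If 13 came from that formula, the stated 80% does not belong to the t-test that the protocol plans. The type 2 error would then be about 26% instead of 20% for NMES versus control, the only contrast for which the protocol gives planning means, even with the planning effect and SD taken as correct.

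**Working it through.** **Inputs, all from the Sample size section except the allocation ratio**

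- Difference: 26.1 − (−8.3) = 34.4
- SD: 24.82 in both groups
- Standardised difference: d = 34.4 / 24.82 = 1.386
- Two-sided alpha 0.0083, which is consistent with 0.05/6 for six pairwise comparisons of four groups
- Target power 80%, dropout 25%
- Equal allocation (Study design section)

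**Step 1: reproduce the plan's figure.** The normal approximation is

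n = 2 (z₁₋α/₂ + z₁₋β)² / d² = 2 × (2.640 + 0.842)² / 1.386² = 12.62, rounded up to 13.

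Under this approximation the nominal power at 13 is 81.4%. The dropout step is 13 / 0.75 = 17.3, so 18 per group and 4 × 18 = 72. The stated chain is reproduced exactly.

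**Step 2: power of the two-sample t-test at 13 per group.** The degrees of freedom are 2 × 13 − 2 = 24. The noncentrality is d × √(n/2) = 1.386 × √6.5 = 3.534. The two-sided critical value at alpha 0.0083 is 2.877, against 2.640 for the normal. The noncentral t distribution gives a power of 73.7%. A simulation of 400,000 trials also gave 73.7%. With alpha taken as exactly 0.05/6 the power is 73.8%.

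**Step 3: sample size for 80% power with the t-test.**

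| Completers per group | Power, two-sample t-test, alpha 0.0083 |
|---|---|
| 13 | 73.7% |
| 14 | 78.2% |
| 15 | 82.0% |
| 16 | 85.3% |
| 18 | 90.4% |

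The unrounded solution is 14.45, so 15 per group. With 25% dropout that is 15 / 0.75 = 20 per group, 80 in total.

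**Step 4: more favourable readings.**

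- Exactly 25% dropout from 72 leaves 54 completers, or 13.5 per group. The t-test then has 76.1% power.
- At 13 per group with the error variance pooled over all four groups (48 degrees of freedom), power is 77.8%.
- With both together (13.5 per group and pooled variance), power is 79.8%.
- Suppose a four-group ANCOVA on baseline is used and 24.82 is the SD of a change score. The residual variance is then multiplied by (1 + r)/2, where r is the correlation between baseline and week 12. At 13 per group (47 degrees of freedom) power is 85.3% for r = 0.7, 80.2% for r = 0.9 and 79.0% for r = 0.95. The protocol gives no value for r, so these values are assumptions.

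**The case against.** The arithmetic is not in dispute. The case against concerns its weight.

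- **There is no single stated test.** The Sample size section names none, and the Statistical methods section lists ANCOVA and a mixed model beside the t-test. The t-test is the least favourable parametric choice. This is fair, and it is why the shortfall should be read as largest for the t-test. But the sizing uses an unadjusted difference and SD with no baseline correlation, so an adjusted analysis cannot be credited with the 80%. Pooling the variance still leaves 77.8% at the stated 13.
- **The shortfall almost vanishes at 13.5 per group with pooled variance (79.8%).** That is true, but the protocol's claim is about 13 completers, not 13.5.
- **Eighteen per group are recruited.** With 15 or more completing (dropout up to 3/18, about 17%), t-test power is at least 82%. This stands and limits the practical harm. The protocol nevertheless plans for 25%.
- **The source of the 13 is inferred.** This also stands. A one-sided t-test at 0.0083 would return 13 too, with 82.2% power, but the protocol specifies a two-sided test. The error does not depend on which route was taken.
- **The Statistical methods section sets significance at 0.05, where 13 per group would give about 92%.** That drops the very correction on which the trial was sized. It is a separate inconsistency and does not support the 80%.
- **The planning effect is itself uncertain.** A standardised difference of 1.39 from one earlier study may well matter more than t against z. That is a reason to keep this point in proportion, not to leave a wrong figure in place.

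**Conclusion.** The concern holds. On the protocol's own inputs, 13 completers per group give 73.7% power for a two-sided two-sample t-test at alpha 0.0083, about 6 points below the stated 80%. Two more completers per group (15) would be needed. The result assumes normal data with a common SD of 24.82 and a true difference of 34.4, as the protocol does. The Wilcoxon alternative would have slightly less power under normality. The shortfall narrows to about 2 points with four-group pooled variance, and it could disappear under baseline adjustment, depending on a correlation that the protocol does not state. This is a correction to the stated power that should be made. It does not threaten the trial's validity.

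**What to change.** In the Sample size section, name the test and state that 13 completers per group give about 74% power for the two-sample t-test at two-sided alpha 0.0083. It would help to add that 80% is reached with 15 completers per group, which the 72 recruited would supply if no more than 3 of 18 per group drop out.

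Alternatively, make the four-group baseline-adjusted ANCOVA both the sizing basis and the primary between-group analysis. The section should then say whether 24.82 is the SD of change, which the negative control mean of −8.3 suggests, and give the assumed baseline-to-week-12 correlation. At 13 per group this gives 80% to 85% for correlations of 0.9 to 0.7, but just under 80% at 0.95.

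The first option costs one corrected and less favourable figure. The second costs a stated assumption and a commitment to one analysis. Neither changes enrolment. Enrolment would rise, to 80, only if 80% power for the unadjusted t-test at 25% dropout were insisted on.

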### Statistical methods

The statistical processing will be performed with PASW advanced statistics (SPSS Inc, Chicago, IL) version 20.0 and according to an intention-to-treat principle. Data will be reported as the mean, standard deviation, and confidence intervals or in percentage frequencies. The Shapiro-Wilk test will evaluate the normal distribution of the variables. Evaluation variables, including muscle strength, performance tests, and questionnaire surveys, will be analyzed at baseline and after 4, 8, and 12 weeks by using paired *t*-tests or Wilcoxon signed-rank tests. Outcomes will be compared between groups by using two-sample *t*-tests or Wilcoxon rank sum tests according to normality. Analysis of covariance will also be conducted. The between-group differences in the outcome measures after the intervention will be calculated using repeated measure mixed models with patients as random effects, and group and time as fixed effects, and adjustments for baseline imbalances. The Spearman rank test or Pearson product-moment correlation coefficient analysis may be used to analyze the associations between clinical data and outcome measures. Statistical significance is set at a *p* value < 0.05. There is no plan for any interim analysis or stopping data collection. There are no planned subgroup analyses for any of the primary or secondary outcomes.

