**Fig. 1 Fig1:**
[figure not shown]
Clinical trial design

The primary endpoint was the difference in hand grip and leg muscle strength at 12 weeks among the 4 treatment groups. Secondary endpoints included the following: muscle mass; physical performance, including the 10-m walking test and timed-up-and-go test; and questionnaires about QOL, physical activity, depression, and falls.

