### Recruitment and population

A total of 72 patients with ESRD receiving HD will be recruited in four tertiary hospitals in Korea.

Subjects will be eligible for inclusion in this study only if all of the following criteria apply: (1) stable ESRD patients who have been receiving HD for 3 months or more, (2) patients with serum albumin less than 4.0 g/dl and are suspicious of having PEW, and (3) patients who can thoroughly understand the protocol.

Subjects will be excluded for any of the following reasons: (1) acute kidney injury; (2) uncontrolled hypertension, diabetes, or heart failure; (3) aspartate aminotransferase (AST) or alanine aminotransferase (ALT) level 3 times or higher than the upper normal limit of the participating hospital; (4) hematologic or solid organ malignancies under treatment; (5) active infection; (6) positive for HIV/AIDS; (7) history of ischemic heart disease, stroke, or deep vein thrombosis within 3 months before participation; (8) planning to receive kidney transplantation within 3 months after participation; (9) contraindication to electronic stimulation including implantable defibrillator; (10) skin lesions around the electrical stimulation spots; (11) allergy to protein supplements; (12) history of participation in another clinical study within 2 months prior to study enrollment and plans to participate in another clinical study; and (13) researcher’s decision regarding inappropriateness of enrollment in the study.

All patients who are eligible for this study will be asked by study investigators. They will receive oral and written information from the investigator. The investigator will obtain written informed consent and the patient will be randomized.

As the participation in the study is voluntary, all participants are free to withdraw their consent to participate in the study at any time and for any reason without any further treatment or any consequences. Moreover, participation of any participants could be terminated by an investigator at any time, if an investigator believes it is in the best interest of the participant. We shall document the reasons and circumstances of the study discontinuation in the clinical record form.

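### No analysis is fixed as primary for week 12: the simple tests use observed cases only, and the mixed model, as written, does not target the week-12 difference

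*Protocol article*

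**What the plan says.** **Endpoint.** Under Study design: "The primary endpoint was the difference in hand grip and leg muscle strength at 12 weeks among the 4 treatment groups". The section on hand grip and leg muscle strength schedules readings at baseline and every 4 weeks, so at weeks 4, 8 and 12.

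**Attrition.** Under Sample size: "13 participants are needed per group to complete the study". The next sentence adds: "To allow a 25% dropout rate, we will initially recruit at least 72 participants". Recruitment and population lets patients withdraw at any time and lets an investigator end a patient's participation.

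**Analysis.** Statistical methods sets the work "according to an intention-to-treat principle". It then names, in order:
- paired tests within groups;
- two-sample t-tests or rank-sum tests between groups, chosen by normality;
- ANCOVA, as an additional analysis;
- repeated-measures mixed models for the between-group differences after the intervention, with patient as random effect, group and time as fixed effects, and an unspecified adjustment for baseline imbalance.

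None of these is called primary, and no group-by-time term is mentioned.

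**The concern.** The primary endpoint belongs to one visit, and three kinds of between-group analysis are offered for it. They differ in which patients they use and in what they estimate.

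A t-test, rank-sum test or ANCOVA on week-12 values uses only patients who have that value, unless missing values are filled in. That sits badly with an intention-to-treat statement when the sample size itself counts completers. No sham stimulation or placebo supplement is described, so patients can tell their arm, and reasons for leaving could plausibly differ between arms. If weaker or declining patients leave one arm more selectively, the remaining patients are no longer comparable.

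The mixed model is the one listed method that can use the week-4 and week-8 readings of patients who leave later. With group and time as main effects only, however, its group coefficient is one difference common to all visits. That is not the week-12 difference unless the effect is the same at every visit. As written, no listed method clearly both keeps early leavers and estimates the stated endpoint.

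**Working it through.** **1. The plan's own numbers.** Inputs from Sample size: means 26.1 and −8.3, so a difference of 34.4; SD 24.82; two-sided alpha 0.0083; power 80%.

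- Normal approximation: n = 2 × (2.640 + 0.842)² × 24.82² / 34.4² = 12.6, so 13 per group.
- Dropout allowance: 13 / 0.75 = 17.3, so 18 per arm; 18 × 4 = 72.

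Both stated figures reproduce. The alpha equals 0.05 / 6, which matches the six pairwise contrasts of four arms. The trial is thus sized on a pairwise comparison of completers.

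**2. Patients in an unimputed week-12 test.** At 25% loss, 0.25 × 72 = 18 have no reading and 54 remain (13.5 per arm). The standard error of a difference is then 24.82 × √(2 / 13.5) = 9.55.

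**3. Possible bias in that test.** This is a simulation. From the document: 18 per arm, 25% dropout, SD 24.82. Assumed: no true effect; random dropout in one arm; in the other, dropout related to a low week-8 change (logistic slope 0.75 to 1.5 per SD); correlation between visits 0.5 to 0.85.

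| Correlation | Slope | Size of completer bias |
|---|---|---|
| 0.5 | 0.75 | 1.97 |
| 0.5 | 1.5 | 3.45 |
| 0.7 | 0.75 | 2.74 |
| 0.7 | 1.5 | 4.77 |
| 0.85 | 0.75 | 3.72 |
| 0.85 | 1.5 | 5.73 |

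- Relative to the standard error: 1.97 / 9.55 = 0.2 to 5.73 / 9.55 = 0.6.
- Relative to the planned difference: 1.97 / 34.4 = 6% to 5.73 / 34.4 = 17%.
- Rejection rate of the nominal 5% test: 4.9% to 9.3%. An independent repeat gave a bias of 2.3 to 5.8 and rejection of 4.6% to 9.7%.
- An estimate that also uses the week-8 value has a bias of at most 0.21.

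In a separate large-sample run (correlation 0.7; in one arm, half of those with a below-average week-8 value leave), the completer difference was off by about 5.0. A mixed model on all visits, fitted with a group-by-visit term, was off by about 0.0.

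**4. What the mixed model estimates without a group-by-time term.** Take the planned 34.4 at week 12 and, as an assumption, a linear build-up: one third at week 4, two thirds at week 8, all at week 12.

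- Responses at weeks 4, 8 and 12, all observed: 34.4 × (1/3 + 2/3 + 1) / 3 = 22.9, or 67% of the week-12 effect.
- Baseline also a response: 34.4 × (0 + 1/3 + 2/3 + 1) / 4 = 17.2, or 50%.
- Responses at weeks 4, 8 and 12, simulated with 25% lost after week 8: about 21, or 21 / 34.4 = 61%. It falls further because fewer week-12 readings enter. Adding a group-by-visit term to the same model recovers 34.4 within simulation error.

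If the full effect were present from week 4, the average over weeks 4, 8 and 12 would be 34.4 and nothing would be lost. If it appeared only at week 12, that average would be 34.4 / 3 = 11.5.

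**The case against.** A reader might infer that the whole plan is a completer analysis under an intention-to-treat label and that a quarter of the patients are certain to be lost from it. The document does not support that.

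- The mixed model stands in the same section. It is the method named for calculating the differences after the intervention, and it can keep patients who leave after week 4 or 8.
- The 25% is a recruitment allowance and not a forecast. The article does not say that every dropout lacks a week-12 reading.
- An imputation rule may sit in the full protocol or the analysis plan. Its absence from an article is not a defect, and the article nowhere says that patients without a reading are excluded.
- It would also go too far to say that the mixed model omits anyone who leaves before week 4. How baseline enters that model is not stated.
- The arm-specific dropout behind the bias figures is assumed, and no passage documents it. At the mild end the error rate does not rise at all.

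All of this stands, and it limits the point. It does not settle which analysis carries the week-12 conclusion. An interaction term may have been lost in condensing the article, but the article does specify the model's fixed effects, and those listed do not yield the stated endpoint.

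**Conclusion.** The point holds in a limited form. Several analyses of one primary comparison are listed without a primary one. Those that address week 12 directly use about 54 of 72 patients if the dropout allowance is reached and nothing is imputed. The one that keeps early leavers is written so that it estimates a visit-averaged difference.

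The size depends on assumptions outside the document. With strength-related dropout in one arm only, the completer bias is about 2.0 to 5.7 units, and the nominal 5% error rate lies between 4.9% and 9.3%. With dropout unrelated to strength, the bias is zero. With a linear build-up and all readings present, the main-effects mixed model reports 22.9 units (17.2 if baseline is also a response) where the week-12 difference is 34.4. With a constant effect from week 4 and baseline not used as a response, it reports the full difference.

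The change is worth making because it is cheap and the needed readings are already scheduled. This is not evidence that the trial's conclusions would be invalid.

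**What to change.** Name the planned likelihood-based mixed model as the primary analysis, for both hand grip and leg strength, and state that:

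- it includes all randomised patients with a baseline value;
- visit is a categorical factor, with a group-by-visit term;
- baseline enters as a response with group means constrained equal, or else as a covariate (the first also keeps patients who leave before week 4; the second does not);
- the week-12 contrasts between groups are the primary estimates.

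Describe the week-12 t or rank-sum tests and ANCOVA as supportive analyses of patients with observed data, not as intention-to-treat.

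The cost is a few sentences in Statistical methods and a little programming, with no extra visits, staff or patients. The downside is reliance on data being missing at random given the observed readings. One delta-adjusted sensitivity analysis, which shifts the unobserved week-12 values unfavourably, would show how far the conclusion depends on that.

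### A Shapiro-Wilk test on the outcome data, with its unit and level unstated, decides whether groups are compared on means or on ranks, although an ungated baseline-adjusted model is already planned

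*Protocol article*

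**What the plan says.** All of the analysis text is in the protocol article under Statistical methods. It states that "The Shapiro-Wilk test will evaluate the normal distribution of the variables". Between-group comparisons then use two-sample t-tests "or Wilcoxon rank sum tests according to normality". The paragraph does not say whether normality is judged in each arm, in each pair of arms or over the whole variable, or at what level.

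Two further between-group analyses follow, and neither depends on the normality result: "Analysis of covariance will also be conducted", and "The between-group differences in the outcome measures after the intervention will be calculated using repeated measure mixed models with patients as random effects", the latter with adjustment for baseline imbalance. None of the three is named as the deciding analysis. On reporting, the same paragraph says that "Data will be reported as the mean, standard deviation, and confidence intervals or in percentage frequencies".

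The Sample size section works from a difference in mean leg strength at an alpha of 0.0083 and concludes that "13 participants are needed per group to complete the study".

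**The concern.** A rule that picks the test from the outcome data leaves the hypothesis open until those data are in. A t-test compares means. A rank sum test compares distributions through ranks, and its natural estimate is not a difference in means. The trial is sized on a mean difference and promises means with confidence intervals, so the rank branch answers a somewhat different question from the one that was powered.

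The gate is also weak at this sample size: with about 13 patients it often misses real skewness and sometimes flags normal data. Since its unit and level are open, two analysts following the text could reach different tests from the same data.

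The two-sample tests have no baseline term. Run on 12-week values, they ignore the baseline strength measured in every patient. The ungated models use it. One outcome could then carry a rank p value beside a mean-based, baseline-adjusted estimate, with nothing to say which counts.

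**Working it through.** **Inputs.** From the Sample size section: means 26.1 and −8.3, SD 24.82, alpha 0.0083 two-sided, power 80%, 13 completers per arm, 25% dropout, 72 recruited. From Study design: four arms at 1:1:1:1, so 4 × 3 / 2 = 6 possible pairs. The six comparisons are not listed, but 0.05/6 = 0.0083 implies them. Assumed, because the article is silent: gate level 5%, and the shape of the outcome distribution.

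**The plan's own figure.** The difference is 26.1 + 8.3 = 34.4. By the normal approximation, n per arm = 2 × [24.82 × (2.640 + 0.842) / 34.4]² = 12.62, so 13. Then 13 / 0.75 = 17.3, so 18 per arm and 72 in total. Both stated figures reproduce.

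**Gate applied per arm** (t-test only if both arms pass). Let p be the chance that an arm fails Shapiro-Wilk.
- No arm fails: all six pairs use the t-test.
- One or two arms fail: tests are mixed.
- Three or four arms fail: all six pairs use Wilcoxon.

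So P(mixed) = 4p(1−p)³ + 6p²(1−p)².
- Normal data, p = 0.048: 0.166 + 0.013 = 0.178.
- Log-normal with sigma 0.5, p = 0.332: 0.396 + 0.295 = 0.691.

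Simulation under the null (20,000 trials, 13 per arm, nominal 5%) agrees:

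| Shape | Arm fails gate | Six pairs mix tests | Error of t-tests that passed | Error of whole rule |
|---|---|---|---|---|
| Normal | 4.8% | 18% | 5.1% | 5.2% |
| Gamma, shape 4 | 18% | 53% | 5.7% | 5.3% |
| Log-normal, sigma 0.5 | 33% | 69% | 6.7% | 5.2% |
| Exponential | 59% | 51% | 9.4% | 5.1% |
| Log-normal, sigma 1 | 75% | 26% | 12.4% | 4.7% |

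At nominal 0.83% the whole rule gives 0.69 to 0.84%. With all 18 recruited patients per arm, mixing is 18.5% (normal) and 65% (log-normal 0.5), and the whole rule stays at 4.8 to 5.4%.

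**Gate applied per pair** (26 values, 10,000 trials). Tests mix in 9 to 75% of trials. T-tests that pass have 3.5 to 5.3% error, and the whole rule 4.4 to 4.9%.

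**Gate applied to the pooled variable** (52 values, 10,000 trials). One test serves all six pairs, so nothing mixes. T-tests that pass run at 4.8 to 5.5%, for the shapes that pass often enough to estimate, and the whole rule at 4.4 to 4.9%. However, pooled raw values contain the treatment effect. Take log-normal (sigma 0.5) data and add the planned shift of 34.4/24.82 = 1.39 SD to both NMES arms, assuming that the combined arm gains as much as NMES alone. Shapiro-Wilk rejection then falls from about 93% without an effect to about 52% with it. With normal data the same shift hardly changes the rejection rate, so this dependence needs skewness.

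**Does the choice matter?** At the planned effect, 13 per arm and alpha 0.0083, the t-test and Wilcoxon disagree on significance in roughly 7 to 14% of comparisons, depending on the shape assumed.

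**The case against.** A reader might infer from the gate that the trial's false-positive rate is inflated. The calculations do not support that: the whole rule stays within 4.4 to 5.4% under every unit and shape tried. The higher error of t-tests that pass (up to 12.4% in the table) is conditional on passing, is seen only when the gate works per arm, and is small for mild skew.

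Nor can mixing be stated as something that will happen. It needs a per-arm or per-pair gate. The article speaks only of the variables, and a single test per variable is at least as natural a reading. With normal data, mixing does no harm to validity.

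A reader might also infer that the six results could not be jointly corrected, or that a rank analysis cannot use baseline or give an answer in kilograms. None of this follows. Bonferroni works with any valid p values, a rank test can be run on change scores, and a Hodges-Lehmann shift with its interval is in kilograms.

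The skewed shapes are assumptions. A planning mean of −8.3 points to change values, for which a log-normal is a poor model. Finally, the mixed model and ANCOVA are already planned without a gate, and log scales or residual plots are ordinary SAP detail, so their absence here is no fault.

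These points limit the size of the concern. They do not remove it: a data-driven choice of test is written into the article as a rule, with its operation undefined, beside models that make it unnecessary.

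**Conclusion.** The concern holds as a matter of analysis choice and interpretability, not of overall error control. The article fixes the choice between means and ranks only after the outcome data are seen and leaves open how the gate operates. Each way of applying it has a cost. Per arm or per pair, the comparisons of one outcome can rest on different tests. On the pooled variable with skewed data, the choice depends on whether treatment works.

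The per-arm mixing figures of 18% and 69% rest on an assumed 5% gate, 13 completers per arm, the same shape in all arms and no treatment effect. The fall in pooled rejection rests on the assumed log-normal shape and an equal shift in both NMES arms. The mismatch with a sample size built on a mean difference, and the absence of a baseline term in the gated tests, need no simulation.

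**What to change.** Delete the normality condition for between-group comparisons. State that every continuous outcome is compared between groups by the baseline-adjusted four-arm model that the plan already contains, whatever Shapiro-Wilk shows, and that its group contrasts and confidence intervals are the reported results. If rank tests are kept, give them for all pairs of an outcome and label them as a sensitivity analysis.

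This is a change of wording, best made before any outcome data are compared by group. It needs no extra patients or measurements, uses baseline values already collected, and reduces the number of analyses. The small downside is that model-based intervals rely on approximate normality, which is less secure for very skewed scales. The rank sensitivity analysis covers that case. The change should not be presented as correcting an inflated type I error, since none is shown.

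### Three between-group analyses of the primary strength outcomes are planned at p < 0.05, and none is named as the one that decides the week-12 endpoint

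*Protocol article*

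**What the plan says.** The Study design section defines the endpoint: "The primary endpoint was the difference in hand grip and leg muscle strength at 12 weeks among the 4 treatment groups". Strength is measured at baseline and at weeks 4, 8 and 12.

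The Statistical methods section gives three between-group analyses of such outcomes:

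- The first and second: "Outcomes will be compared between groups by using two-sample *t*-tests or Wilcoxon rank sum tests according to normality. Analysis of covariance will also be conducted". For the second, covariates and time point are not given.
- The third: "The between-group differences in the outcome measures after the intervention will be calculated using repeated measure mixed models with patients as random effects". Group and time are the fixed effects, with adjustment for baseline imbalances. No group-by-time term is mentioned.

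One threshold follows: "Statistical significance is set at a *p* value < 0.05". No analysis is called primary, supportive or sensitivity.

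The Sample size section works at a different level: "an alpha value of 0.0083 due to the correction for type 1 error according to multiple tests, and a desired power of 80" per cent.

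**The concern.** The three analyses answer related but different questions and can disagree. A two-sample test may or may not take account of baseline, depending on whether it is applied to week-12 values or to change. ANCOVA normally adjusts for baseline. A mixed model with only group and time main effects estimates a group difference averaged over follow-up visits, whereas the endpoint is at week 12.

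If the three p-values differ, the plan does not say which one settles the primary question. The conclusion could then be chosen after the results are seen, and the stated error rate would not describe the procedure actually used. Tightening the threshold would not by itself remove this, because there would still be three chances per comparison.

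**Working it through.** **The plan's own figure.** The Sample size section gives means 26.1 and −8.3 (difference 34.4), SD 24.82, two-sided alpha 0.0083 and 80% power.

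- n per group = 2 × (z₀.₉₉₅₈₅ + z₀.₈₀)² × SD² / difference² = 2 × (2.640 + 0.842)² × 24.82² / 34.4² = 12.6, rounded up to 13.
- With 25% dropout: 13 / 0.75 = 17.3, rounded up to 18 per group; 18 × 4 = 72.

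Both figures match the article. Four arms give six pairs, and 0.05 / 6 = 0.0083. The sizing therefore assumes a correction for six pairs on one outcome, which the 0.05 in Statistical methods does not carry forward.

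**Error under no effect.** The check is a simulation of null trials with normal data, four arms of 13 or 18, six pairs and two outcomes. Three inputs are assumptions, because the article does not give them:

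- correlation between visits of 0.5 to 0.9, compound symmetry or AR(1);
- correlation between the two outcomes of 0 or 0.5;
- the rule that any analysis below the threshold counts as a difference.

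Two readings of the text were varied: the two-sample test on week-12 values or on change, and the mixed model averaged over weeks 4, 8 and 12 or read at week 12. In the second case it nearly duplicates the week-12 ANCOVA and was treated as the same test.

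Examples at visit correlation 0.8 with uncorrelated outcomes:

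| Rule | One comparison | Six pairs, one outcome | Six pairs, both outcomes |
|---|---|---|---|
| One analysis, 0.05 (18 per arm, AR(1)) | 5% | 21% | 37–38% |
| Any of three, 0.05, model averaged (18 per arm, AR(1)) | 10% | 36% | 58% |
| Any, 0.05, model at week 12, raw values (13 per arm) | 8.6% | 33% | 55% |
| Any, 0.05, model at week 12, change scores (13 per arm) | 6.4% | 25% | 44% |
| One analysis, 0.0083 (18 per arm, AR(1)) | 0.8–0.9% | 4% | 8% |
| Any of three, 0.0083, model averaged (18 per arm, AR(1)) | 1.8% | 8.5% | 16% |

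Across all settings at 0.05:

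- Model averaged over follow-up: 8.4–12.1% per comparison and 50–67% over both outcomes.
- Model read at week 12: 6.3–9.3% and 40–58%.
- One analysis only: 5% and about 32–38%.

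Across all settings at 0.0083, over both outcomes: about 13–20% with the averaged model, 10–15% in the near-duplicate case, and 7–9% with one analysis.

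**Where the total comes from.** In the 18-per-arm example, one analysis already gives 0.368 to 0.377 of the 0.577, which is 64% to 65%. Six pairs and two outcomes tested at 0.05 therefore account for most of the total. The choice among methods adds the rest.

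**The case against.** A reader might infer that the plan has an 11% error per comparison and declares a difference about 60% of the time when nothing works, and that the three methods cause this. The documents do not support that reading, for three reasons.

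- **The rule is assumed.** Nowhere does the article say that one significant analysis suffices. It lists methods and a level.
- **The figures depend on the reading.** About 11% and 60% arise with raw week-12 values and compound-symmetry correlations near 0.7–0.8. The sizing mean of −8.3 cannot be a strength value, which suggests comparison of changes. With change scores and a week-12 model the rates are nearer the low end.
- **Attribution.** About 35% remains with a single analysis at 0.05.

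The loss of precision from an unadjusted test also depends on the reading. At baseline correlation 0.75, the ANCOVA standard error is √(1 − 0.75²) = 0.66 times that of a raw week-12 t-test, but √((1 + 0.75)/2) = 0.94 times that of a change-score test.

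It can also be said that ranking analyses belongs in an analysis plan that is not shown, and that the mixed-model sentence hints at a hierarchy. This carries some weight, since an unseen plan may settle the matter. But the article is not silent. It commits to three analyses under one threshold, and the two-sample sentence is worded as firmly as the mixed-model one. That is a rule fixed badly, not a detail left out.

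**Conclusion.** The point holds as a gap in the decision rule. The article fixes three between-group analyses at p < 0.05 and does not say which decides the week-12 primary endpoint. If any significant result were accepted, one comparison would carry about 6–12% error instead of 5%. The whole primary family would carry about 40–67% instead of about 32–38%. These are ranges under an assumed rule and assumed correlations, not properties of the plan as written.

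The unnamed analysis and the threshold have to be settled together. Naming one analysis but leaving 0.05 keeps roughly 35% over both outcomes. Using 0.0083 but leaving three analyses gives about 10–20%. One analysis at 0.0083 per pair gives about 4% for one outcome and 7–9% over both.

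**What to change.** In Statistical methods:

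1. Name one decisive analysis for the primary endpoint: the baseline-adjusted between-group contrast at week 12 from the mixed model, with group-by-time terms added. It should not be treated as interchangeable with ANCOVA. With 25% dropout allowed for, a complete-case ANCOVA loses patients without a week-12 value, while the mixed model uses their earlier visits.
2. Label the two-sample tests and ANCOVA as supportive, reported as estimates with confidence intervals and without a significance claim.
3. Carry the 0.0083 from Sample size into the threshold for the decisive analysis, and state whether it covers both hand grip and leg strength. If either outcome alone could support the conclusion, a Bonferroni level for twelve tests would be 0.05 / 12 = 0.0042. That is stricter than the level used for sizing and would cost some power.

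The cost is a few sentences, with no extra patients, visits or measurements. Recruitment was still open at publication, so a dated clarification before the data are analysed remains credible. The small downside is that a significant supportive analysis could no longer be claimed as a primary finding.
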